#### Neuroimaging outcomes

2.4.2.

*Brain connectivity* of fronto-temporal brain networks will be derived from resting-state fMRI. Six seed areas will be used as the primary neuroscientific outcome. Seeds are anatomically defined regions of interest (ROIs) in Montreal Neurological Institute (MNI) space for the *left and right Heschel’s Gyri, Inferior Frontal Gyri, and Temporal Poles*. These seeds form part of fronto-temporal brain networks involved in language and communication that may be altered in ASD and modified by MT (29).

*Structural brain changes,* grey and white matter volume, will be assessed using whole-brain voxel-based morphometry (VBM), derived from the structural T1-weighted image acquired at the beginning of each scanning procedure.

#### Biological outcomes

2.4.3.

*Chronic stress* will be measured through hair cortisol concentration in the scalp-nearest 3 cm segment, reflecting cumulative cortisol secretion over the past 3 months (69). Chronic stress was suggested by M4A user representatives during the development of the initial protocol and is relevant to MT (46) and ASD (10). For determination of hair cortisol concentration, the first scalp-near 3 cm segment will be used which is thought to reflect the cumulative cortisol secretion of the past 3 months (70). Hair wash and cortisol extraction procedures are based on a laboratory protocol by Stalder et al. (69), with minor modifications (71). For cortisol determination, a commercially available cortisol luminescence immunoassay will be used (LIA; IBL International, a Tecan Group company, Hamburg, Germany). Inter- and intra-assay coefficients of variation will be computed.

*Gut microbiome data* will be collected from stool samples to investigate the relationship between the profile of gut microbial composition in children with ASD and brain structure and function and if music therapy influences the gut microbiome composition. The “gut-brain-axis” is thought to provide a bidirectional pathway of communication between the gut microbiome, brain function, and behavior, routed via the vagus nerve and other mechanisms (72–74). ASD is often associated with gastrointestinal problems and gut microbiota dysfunction (75). How the gut-brain axis affects cognitive function is unclear; an informed cognitive neuroscience perspective on this matter is so far missing. To account for factors potentially affecting gut microbial composition, we will also ask whether participants experienced intestinal illness and/or have taken antibiotics in the last 3 months, the individual’s body-mass index, dietary habits, as well as the frequency and timing of bowel movements. The microbial community composition in collected stool samples will be determined by 16S rRNA gene amplicon sequencing (76). The resulting data will be taxonomically classified and submitted to analyses using common bioinformatics pipelines implemented in R (77).

#### Additional measures

2.4.4.

Demographics (age, gender, and socioeconomic status) and developmental history will be collected at baseline.

*Adverse effects* of MT are rare (11, 30), but will be collected throughout the study. After each intervention, parents will be asked if any serious or non-serious adverse events occurred since the previous assessment, irrespective of their connection to the study procedures. Parents will also be requested to provide a detailed description of any adverse events encountered.

*Participant preferences* will be recorded by asking parents at the last follow-up to ask their children which intervention they preferred, to what degree, and why. The ability to directly compare preferences is unique to crossover trials and may yield important additional information (78, 79).

### Scanning parameters

2.5.

Both sites will use 3 T scanners (Bergen: GE Signa HDx, Vienna: Magnetom Skyra by Siemens Medical), equipped with a 32-channel head coil and a high-performance gradient system for fast, high-resolution whole-brain multiband echoplanar imaging. Resting-state EPI images will be obtained in 54 slices with voxel dimensions of 2.39 × 2.39 × 2.4 mm, covering the whole brain (TR = 800 ms, TE = 3.7 ms, matrix size, 88 × 88; field of view [FOV] 210 mm; flip angle 52°). Seven hundred and fifty volumes will be obtained in 10 min; additionally, participants will complete a high resolution sagittal T1-weighted structural scan (voxel dimensions: 1.2 × 1.05 × 1.05 mm, reduction factor of 2) with a duration of 6 min and 45 s. Acquisition protocols will be harmonized across sites and aligned with the ENIGMA ASD working group (e.g., duration of resting state ≥8 min).

### Study procedure

2.6.

Assessments at the four planned time points will be conducted during two in-person visits and through questionnaires administered electronically to parents and teachers. Assessments will include demographic data and developmental history (only at baseline), psychometric, neuroimaging, and biological assessments (Table 1). Assessments will be conducted by adequately qualified staff, separate from intervention providers.

During the first visit, children will complete a brain scan and parents will receive a stool sampling kit to be delivered back to researchers on the second visit. The sampling kit consists of a sterile tube, a feces catcher to prevent stool from coming in contact with water or detergents, one-way latex gloves, a Styrofoam box and thermal packs for transport. Stool samples will be collected by participants (with help of the parents if needed), using the materials provided to them by the research team. The sampling kit is specially designed for stool sampling, is widely employed, and is easy to use.

The brain scan procedure requires children to be as still as possible for approximately 16 min inside the MRI scanner. To facilitate the procedure, children will be allowed to watch movies during the scan – an entertaining movie (Tom and Jerry or a preferred movie) during the preparatory scans, structural T1-weighted scan, and breaks between scans, and a specifically designed video (80) during the resting state sequence of the scan that lasts 8 min. To help families prepare, we will provide parents with a movie showing the scanning environment and procedures, a recording of the sounds the scanner makes, and an individualized visual schedule showing the steps to follow on the day of the visit (Supplementary Figure S1).

On the day of the scan, researchers will maintain a calm and patient attitude to facilitate the experience and collaborate with radiographers about any specific details concerning the child. After the visit, children will receive a toy set of an MRI scanner which they can use to role-play visiting the scanner. When needed, we will also offer the option of meeting at the scanning facility prior to the baseline scan to familiarize children with the environment and the researchers.

During the second visit, children will complete a vocabulary assessment and two behavioral prediction tasks. Hair samples will be collected during this visit as well by cutting several thin hair strands as close as possible to the scalp from the posterior vertex region of the head. If a child does not want their hair to be cut, researchers will not collect the hair sample.

### Statistical analysis

2.7.

#### Power calculation

2.7.1.

We designed M4A to be powered for an effect size of *d* = 0.34. Sharda et al. reported a mean difference of 4.84 and an effect size of *d* = 0.34 (SD not reported but calculated as 4.84/0.34 ≈ 14.2) on the CCC-2. Our previous Cochrane review showed similar effect sizes (81). We further assumed outcomes for MT and PT to be correlated with *r* = 0.50. With a two-sided significance level of 5%, a sample of *n* = 70 will be required for 80% power; to accommodate for attrition, we plan to recruit 80 participants. Similar power can be achieved for a range of reasonable effect sizes and correlations (Figure 3). The same power can be reached with varying combinations of effect sizes, correlations, and numbers of participants with complete data; in contrast, a parallel design would require almost 300 participants (Supplementary Table S2).

**Figure 3 fig3:**
[figure not shown]
Power calculation for the primary outcome.

#### Data analysis plan

2.7.2.

Statistical analysis of all outcomes will be on an intention-to-treat (ITT) basis. In contrast to Sharda et al. who used a parallel design, special considerations apply to crossover trials. All continuous outcomes (whether psychometric, neuroimaging, or biological) will, following a graphical examination of normality, compare the post-test difference between interventions within each participant, adjusted by the difference in pre-tests within each participant in an ANCOVA model. This approach is optimal for crossover trials with baseline measurements, both in terms of making best use of baseline measures to improve precision, and in avoiding bias from randomly occurring baseline imbalance (82). The model can be written as follows:

$$\left(Y_{Ti}-Y_{\mathrm{Ci}}\right)=\beta_{T}+\gamma \left(X_{Ti}-X_{\mathrm{Ci}}\right)$$

for participant *i*, where *Y* is the post-test, *X* is the pre-test, *T* is the treatment and *C* is the control condition; the intercept β_T_ then represents the treatment effect and *γ* represents the influence of the baseline measurement (82). Sensitivity analyses will include age and functioning level as additional covariates. A further sensitivity analysis will include therapists as random effects.

The intention-to-treat principle will be followed as applicable in a crossover trial (79). Participants will be analyzed in the group to which they were randomized, regardless of whether they received the full allocated intervention. However, participants can only be analyzed if they have data for all time points for the respective outcome. This leads to two possible analysis strategies: (a) to include only participants with valid data for both intervention periods (complete case analysis); or (b) to impute values for missing values (either through multiple imputation based on known variables; or, as a simpler approach but with less desirable statistical properties, baseline values of the same outcome, known as last observation carried forward, LOCF). Sharda et al. used LOCF (personal communication, [name], 4 April 2022). We aim to use complete case analysis as the main strategy unless the rate of missing data is high. If a complete case analysis results in a high proportion of missing cases (e.g., > 10%), we will consider an imputation strategy.

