#### Enrollment and randomization

2.2.2.

When possible, enrollment will be scheduled so that interventions will take place during the school year and washout periods during school holidays. We expect to randomize around 27 participants each half year in both sites combined. Computer-generated randomization lists, with randomly varying block sizes of 4–6, separate for each country, will be used to ensure both unpredictability and balance. The lists will be generated by a researcher who does not have contact with participants and are stored centrally, concealed from clinical investigators, until a decision on inclusion is made. Once a participant is enrolled, the randomization result will be conveyed to clinical investigators through an online system (Research Electronic Data Capture (REDCap) on Norwegian Research Centre (NORCE) servers).

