### Strengths and limitations of the study design

3.2.

An important strength of M4A is its randomized design, which allows for causal conclusions and is considered the gold standard design for evaluating intervention effects. The crossover design implemented in M4A offers the advantage of requiring fewer participants to attain sufficient statistical power while allowing for the examination of individual preferences based on their experience with both interventions (79). However, it should be noted that children are not asked directly about their preferences, but rather parents are asked to report their child’s preferences. Moreover, crossover designs require certain assumptions that can be challenging to assess, including the chronicity and stability of the condition, reversibility of outcomes, and the duration of intervention effects. Although ASD is a lifelong condition, associated behaviors may not remain constant over time, particularly in children. Furthermore, the interventions are hoped to lead to lasting learning effects, which can potentially impact the comparability of the second baseline to the initial one. Moreover, the relative benefits of each intervention may depend on the order in which they are received.

However, we aim to mitigate these issues by implementing a relatively long wash-out period that matches the intervention duration. A practical consideration is the extended timeframe required for each participant, as families might be more motivated to participate in a study where they have the opportunity to receive both interventions compared to a parallel study where their preferred intervention may not be available.

An additional limitation of the study design is that the duration of the interventions might not be sufficient to observe changes. However, given that the study by Sharda et al., which the M4A trial aims to replicate, found effects on functional brain connectivity, family quality of life, and social communication, following 8–12 weeks of music intervention, we expect to replicate these findings. Additionally, a large multinational RCT on music therapy for children with autism, the TIME-A (30), evaluated dosage effects and found no effect of increased duration of interventions on the outcome measures. However, it is important for further studies to assess if a dosage effect is observed, particularly when integrating outcomes from multiple domains, such as functional connectivity and other biological outcomes.

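### The crossover ANCOVA has no period (sequence) term: a net period effect would cost power and, if completers are unbalanced by sequence, cause a small bias

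*Protocol article*

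**What the plan says.** The Data analysis plan (2.7.2) states the model as an equation. For each child, the post-test under music therapy (MT) minus the post-test under play therapy (PT) is regressed on an intercept and on the matching pre-test difference; in its words, "adjusted by the difference in pre-tests within each participant in an ANCOVA model". The intercept is the treatment effect. The section applies this to every continuous outcome. Its sensitivity analyses add age and functioning level, and then therapist as a random effect. None adds period or sequence. The RSFC and VBM models in 2.7.3 list intervention, age and IQ with either baseline RSFC or total intracranial volume, and again no period.

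The section on strengths and limitations (3.2) allows that "associated behaviors may not remain constant over time, particularly in children", that learning may carry into the second baseline, and that relative benefit may depend on order. The design answer it gives is the long wash-out. Under 2.2.2, and only when possible, enrolment is arranged so that "interventions will take place during the school year and washout periods during school holidays".

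**The concern.** MT minus PT is period 1 minus period 2 for children in the MT-PT sequence, and period 2 minus period 1 for children in PT-MT. Anything that shifts scores between the periods, such as maturation or familiarity with the scanner and tasks, enters the outcome with opposite signs in the two sequences. A wash-out deals with carryover. It does not remove a period effect. Period 2 starts six months after period 1, in children aged 6–12.

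Sequence is the factor that is randomised, so it is known for every child. Leaving it out puts systematic between-sequence variation into the error term. It also makes the treatment estimate depend on how many children from each sequence are analysed. Blocked randomisation balances those randomised, but the main strategy is complete cases, so balance among those analysed is not assured. The article fixes the equation itself, so this is not a detail left to a later analysis plan.

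**Working it through.** **Inputs from the protocol (2.7.1).** The trial is "powered for an effect size of *d* = 0.34". The CCC-2 SD is 14.2 points ("SD not reported but calculated as 4.84/0.34 ≈ 14.2"). On correlation: "We further assumed outcomes for MT and PT to be correlated with *r* = 0.50". On size: "With a two-sided significance level of 5%, a sample of *n* = 70 will be required for 80% power"; and "to accommodate for attrition, we plan to recruit 80 participants".

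**The plan's own figure.** SD of the difference = √(2 × (1 − 0.5)) = 1 SD. The normal approximation gives n = ((1.96 + 0.84)/0.34)² ≈ 67.9, or 68. With the noncentral t, n = 70 gives 80.1% power. The stated n reproduces.

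**Algebra.** Let pY and pX be the period 2 minus period 1 shifts in post-tests and pre-tests, in SD units. The net effect is p = pY − γ·pX. The expected adjusted difference is τ − p in MT-PT (n1 children) and τ + p in PT-MT (n2 children). Without a sequence term:

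- expected estimate ≈ τ + p × (n2 − n1)/n
- residual variance at balance ≈ 1 + p², relative to 1

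**Power at 35/35, post-test-only shift, pre- and post-test differences uncorrelated (so γ = 0 and p = pY).**

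| p (SD) | CCC-2 points | variance factor | power from the variance formula |
|---|---|---|---|
| 0.1 | 1.4 | 1.01 | 79.7% |
| 0.2 | 2.8 | 1.04 | 78.5% |
| 0.3 | 4.3 | 1.09 | 76.6% |
| 0.5 | 7.1 | 1.25 | 70.8% |

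Simulating the written ANCOVA (4,000 runs per setting) gives 76.9% without the term against 79.6% with it at 0.3 SD, and 72.3% against 79.8% at 0.5 SD. The formula slightly overstates the loss at 0.5 SD. At balance the estimator itself is no more variable; it is the model's standard error that is too large, so the test is conservative.

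**The mild end: same shift in pre- and post-tests, difference correlation 0.5 (so γ ≈ 0.5 and p is about half the shift).** At 35/35 and 6,000 runs, power is 89.1% without the term against 89.4% with it for 0.3 SD, and 88.1% against 89.5% for 0.5 SD.

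**Bias for a 0.3 SD shift.**

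- 37/33, post-test only: 0.3 × 4/70 = 0.017 SD. Shift in both tests: 0.15 × 4/70 ≈ 0.009 SD (simulated about 0.008).
- 40/30, post-test only: 0.3 × 10/70 = 0.043 SD (simulated estimate 0.295 instead of 0.34). Shift in both tests: 0.15 × 10/70 ≈ 0.021 SD (simulated estimate 0.321).

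In CCC-2 points the largest of these is 0.043 × 14.2 ≈ 0.61, against a target of 4.84.

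**How likely is imbalance?** If ten losses fall at random on 40/40, the split is no worse than 37/33 with probability about 91%. All ten fall in one sequence with probability about 0.1%.

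**Cost of the term with no period effect.** Simulated power is about 79–80% with or without it.

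**The case against.** The strongest reply is that the planned baseline adjustment already does much of this work. With assessments at 0, 3, 6 and 9 months, a linear trend moves the second pre-test as far as the second post-test. If pre- and post-test differences are well correlated, little is left in the residual. This stands, and it is why the loss starts near zero. It needs both conditions. With uncorrelated differences, a 0.5 SD shift in both tests still gives 74.2% against 80.2%. With correlation 0.5, a post-test-only shift of 0.5 SD still gives 83.8% against 90.0%.

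Four stronger readings are tempting, and the document does not support them.

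- **That the protocol expects a period effect.** It says only that behaviours may change. The scheduling in 2.2.2 is an attempt to keep both interventions in school time, not evidence of an effect.
- **That every period effect matters.** Only the net part does. If the CCC-2 composite, a standard score, is normed by age (an assumption), ordinary maturation moves it less than outcomes without such norms.
- **That the primary result will be biased.** This needs imbalance among those analysed. The direction depends on which sequence loses more: at 30/40 with a 0.3 SD post-test shift the estimate rises to about 0.38 and power to about 86%. Nothing in the protocol predicts dropout that differs by sequence. Ten losses from 80 (12.5%) would also pass the 10% level at which imputation is to be considered, so a 40/30 complete-case analysis might not be the one run.
- **That false positives increase.** At balance the opposite holds.

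**Conclusion.** The point holds as a modest, avoidable weakness in a model that the article fixes. The equation and its sensitivity analyses omit period, and both consequences follow: lost power at balance, and bias when completers are unbalanced by sequence. Because no period effect is given, the size can only be a range. At 35/35 the power loss is near zero when the shift is common to pre- and post-tests and their differences correlate at 0.5. It reaches about 3 points (0.3 SD) or 8 points (0.5 SD) when the shift affects post-tests only and the differences are uncorrelated. Bias for a 0.3 SD shift is about 0.01–0.02 SD at 37/33 and 0.02–0.04 SD at 40/30, in either direction. This does not show that the trial is underpowered or that its primary estimate will be wrong.

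**What to change.** Write the model as `(Y_T − Y_C) = beta_T + pi·S + gamma·(X_T − X_C) + error`, with `S = +1/2` for MT-PT and `−1/2` for PT-MT. Because S is centred, `beta_T` remains the treatment effect, and it no longer depends on how many children complete each sequence.

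The difference equation does not carry over directly to the RSFC and VBM models in 2.7.3, which take the post-intervention value as outcome. There, add period as a covariate instead.

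The cost is one degree of freedom and a line of text. No new data are needed, and there is no measurable power loss if no period effect exists. One limit should be noted: a single pooled term will not remove seasonal effects that reverse between enrolment cohorts starting half a year apart.

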#### Neuroimaging data analysis

2.7.3.

Resting-state fMRI data will be preprocessed prior to statistical analysis. Preprocessing steps will include realignment with correction of susceptibility distortion interactions, slice timing correction, outlier detection, direct segmentation, normalization to MNI, and smoothing. We will examine the quality of fMRI scans using visual inspection and framewise displacement (FD) (83), an indicator of head motion, which is a common problem especially in children and clinical populations (84). Volumes exceeding a certain FD threshold [0.5 mm (83) or other values (85)] can be down weighted or scrubbed to obtain usable data (83); longer passages of high movement can be removed.

To examine resting-state functional connectivity (RSFC), the timeseries for each of the six seeds selected will be regressed against all other voxels timeseries in the brain to generate individual participant-level connectivity maps, using whole-brain general linear models at baseline and after the interventions. These first-level maps will then be entered into the second-level analyses. For comparison after the intervention, we will use ANCOVA with post-intervention RSFC as a dependent variable, and intervention, baseline RSFC, age, and IQ as covariates. Z-scores of parameter estimates will be used to measure connectivity strength. Results will be reported with a 5% significance level adjusted for multiplicity by familywise error rate.

To examine the relation between RSFC and behavior change, Z-statistics for each participant from the post-intervention RSFC maps will be used in a linear regression model to evaluate correlation between RSFC and behavior change. All tests will use a two-sided 5% significance level. The two main secondary psychometric outcomes, participation, and quality of life will be Bonferroni-corrected; the remaining secondary outcomes will be exploratory.

To examine structural brain changes images will be segmented into grey- and white-matter probability maps, and a voxel-wise whole-brain statistical analysis will be applied to detect any changes in grey and white matter volume. Preprocessing will include reorientation to the anterior–posterior commissure, normalization to template space, segmentation into tissue types (grey matter (GM), white matter (WM) and cerebrospinal fluid (CSF)), calculation of total intracranial volume and smoothing. Because the participant group is pediatric, as recommended in the CAT12 manual (86), the use of custom tissue probability maps and a custom DARTEL template will be explored. For statistical analyses, we will use ANCOVA with post-intervention grey and white matter volume as dependent variables and intervention, total intracranial volume, age, and IQ as covariates. Participants’ relative GM and WM volume changes will be assessed at a threshold of *p* < 0.05 and will be corrected for multiple comparisons (family-wise error).

Analysis software will be R (77), SPM12 on MATLAB (87) for standard preprocessing, the CAT12 toolbox and DARTEL tools in SPM12 for analysis of VBM, and CONN for denoising and RSFC analysis.

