### Participants

2.2.

Inclusion criteria are being 6–12 years old and having an ASD diagnosis from a licensed health professional with an ICD code (54), ideally supported with scores of standardized tools [ADOS (55), ADI-R (56)] and assessment of intelligence quotient (IQ) or level of ability. Exclusion criteria include individual MT during the last 6 months; generalized epileptic seizures during the last 12 months; more than 12 months of cumulative music training; or conditions precluding fMRI scanning (such as metallic or electronic implants, claustrophobia, hyperacusis, or persistent problems in complying with scanning procedures).

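### Sections 2.7.2 and 2.7.3 prescribe incompatible primary models for the co-primary connectivity outcome, and the 2.7.3 model, read as written, gives up the within-child pairing and requires an optional IQ score

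*Protocol article*

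**What the plan says.** Section 2.4 (Outcome measures) names two primary outcomes, social communication (CCC-2) and functional brain connectivity.

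Section 2.7.2 (Data analysis plan) sets one model for everything continuous: "All continuous outcomes (whether psychometric, neuroimaging, or biological) will, following a graphical examination of normality, compare the post-test difference between interventions within each participant". The covariate is the corresponding within-child difference in pre-tests, and the intercept is the treatment effect. Age and functioning level enter only as sensitivity covariates.

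Section 2.7.3 (Neuroimaging data analysis) describes the second-level RSFC comparison differently: "we will use ANCOVA with post-intervention RSFC as a dependent variable, and intervention, baseline RSFC, age, and IQ as covariates". It adds: "Results will be reported with a 5% significance level adjusted for multiplicity by familywise error rate". It mentions no participant, period or site term. The structural (VBM) analysis in the same section has the same form, with total intracranial volume in the model and no pre-intervention volume.

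Section 2.2 (Participants) requires a diagnosis that is ideally, not necessarily, supported by standardised scores and "assessment of intelligence quotient (IQ) or level of ability". Section 2.5 (Scanning parameters) lists two vendors, one per site: "Bergen: GE Signa HDx, Vienna: Magnetom Skyra by Siemens Medical".

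Section 2.7.1 (Power calculation) states: "We designed M4A to be powered for an effect size of *d* = 0.34". It derives that value from the CCC-2 result of the previous trial and assumes a correlation of 0.50 between a child's two outcomes.

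**The concern.** A co-primary outcome should have one primary model. Here the two prescriptions differ in the response (a difference or a level), in the parameter that carries the treatment effect (an intercept or a coefficient), in the status of age and ability (sensitivity or main model), and possibly in which children can be analysed. With both in print, the choice could be made after the maps have been seen.

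Efficiency is also at stake. The crossover needs about 70 complete children, against almost 300 for a parallel design by the plan's own account, because each child serves as his or her own control. A model that enters post-intervention maps with an intervention covariate and no child term does not use that feature.

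Finally, an IQ score is needed for the 2.7.3 model but not for entry into the trial.

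**Working it through.** **1. Are the two models the same model in different words?**

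- Under 2.7.2 each child contributes one row: post-test after music minus post-test after play. Intervention has been differenced out, so it cannot also be a covariate.
- Under 2.7.3 intervention is a covariate, so each post-intervention map is a separate row.
- A level model with a participant effect could recover the pairing, but none is stated. With fixed child effects, characteristics that are constant within a child, such as an IQ score taken once, cannot be estimated. Listing IQ therefore points to a between-child model, or to an unstated random child effect.

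The models are different.

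**2. The plan's own sample size.** Inputs from 2.7.1: d = 0.34, r = 0.50, two-sided 5%, 80% power.

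- SD of the within-child difference, in SD units: √(2(1 − 0.5)) = 1, so the standardised paired effect is 0.34.
- Normal approximation: ((1.960 + 0.842)/0.34)² ≈ 68.
- Noncentral t: n = 70, power 0.801.
- Attrition: 70/80 leaves 12.5% for loss.

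The stated 70 and 80 reproduce. They are CCC-2 figures under a paired comparison.

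**3. What 2.7.3 would do if run without a child term.** Assumptions: a single univariate test, the CCC-2 effect size, unit variance, and r = 0.5 between all four assessments (the plan gives r only for the two outcomes). Age and IQ are left out; any between-child variance they explain would narrow the gap.

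| Quantity | Formula | At r = 0.5, n = 70 | SE |
|---|---|---|---|
| Variance, 2.7.2 model | 2(1 − r)/n | 1.00/70 | 0.120 |
| Variance the unpaired ANCOVA reports | 2(1 − r²)/n | 1.50/70 | 0.146 |
| Variance the unpaired estimate really has | 2(1 − r)(1 + r²)/n | 1.25/70 | 0.134 |

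- Reported SE against the paired SE: √1.5 = 1.22, or 22% larger.
- Reported SE against its own true SD: √(1.5/1.25) = 1.10, or about 10% too large.
- Type I error: P(|Z| > 1.96 × 1.095) = P(|Z| > 2.147) ≈ 0.03.
- Power: P(Z > 2.147 − 0.34/0.134) ≈ 0.65.

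Simulation with 3,000 runs per setting agrees: power 0.805 paired and 0.657 unpaired; type I error 0.047 and 0.033.

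**4. Sensitivity to the assumed correlations** (simulated power, n = 70, d = 0.34):

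| Pre–post r | Between-period r | Paired | Unpaired | Loss (points) |
|---|---|---|---|---|
| 0.5 | 0.5 | 0.805 | 0.657 | 15 |
| 0.6 | 0.5 | 0.813 | 0.713 | 10 |
| 0.7 | 0.6 | 0.897 | 0.813 | 8 |
| 0.5 | 0.3 | 0.693 | 0.637 | 6 |
| 0.7 | 0.5 | 0.865 | 0.813 | 5 |
| 0.7 | 0.3 | 0.818 | 0.795 | 2 |

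Unpaired type I error was 0.033 to 0.043 throughout.

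**5. Scanner.** With an assumed additive shift of 1 SD between scanners and all correlations 0.5, unpaired power is 0.607 and paired power 0.801. The shift cancels in the difference, provided each child stays on one scanner.

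**6. IQ.** The share of children without a score is not given. If 10%, 20% or 30% of 70 completers lacked one and were dropped, 63, 56 or 49 would remain. Paired power at d = 0.34 and r = 0.5 would be about 76%, 71% or 65%. The shares are assumptions.

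**The case against.** The strongest reply is that 2.7.2 governs. It names neuroimaging, and it says that a crossover needs special handling, unlike the previous parallel-group trial. On this view 2.7.3 is shorthand in a condensed article, and a participant effect may simply have been left out. That stands in part: the text never says that a child's two maps are treated as independent, so loss of pairing is an inference from silence. It does not remove the contradiction, because the response, the treatment parameter and the status of age and ability still differ.

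Several stronger readings are tempting but unsupported:

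- **That the trial's power or sample size is wrong.** No RSFC power is stated, and the only figure given reproduces. The 65% against 80% borrows a CCC-2 effect for a single test, whereas the planned analysis covers whole-brain maps from six seeds with familywise correction. It shows the direction and rough size of a loss; it does not forecast RSFC power.
- **That false positives rise.** In every setting tried the unpaired test was conservative.
- **That different scanners bias the result.** The documents plan harmonised acquisition, and an additive scanner effect cancels under 2.7.2. The scanner issue follows from the model conflict and is not a separate fault.
- **That the missing period term is part of the conflict.** The 2.7.2 model has none either. Sequence is randomised in blocks within country, so sequences should be near balance and a period effect should largely cancel.
- **That children without IQ will certainly be lost.** Handling of a missing covariate is not described and is commonly left to an analysis plan. The text shows only that the score is optional at entry.

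**Conclusion.** The concern holds as a contradiction between two sections over the primary model for a co-primary outcome, and this can be established from the protocol alone.

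The statistical cost is conditional. It arises only if 2.7.3 is followed as written, with no child term, and it is then a loss of efficiency: at worst about 15 points of power among the settings examined, and as little as 2, with a type I error of about 3% to 4% where 5% is nominal. These figures rest on assumed correlations, an effect size from another outcome and a univariate test without age or IQ. Exclusion of children for lack of an IQ score is possible, but its extent is unknown.

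**What to change.** In 2.7.3, make the 2.7.2 model the single primary second-level RSFC model: the within-child difference between the post-music and post-play maps as response, the matching pre-intervention difference as covariate, and the intercept as treatment effect. An equivalent repeated-measures model with a participant effect would also serve. Move age and IQ or functioning level to sensitivity analyses, as 2.7.2 already does. Align the VBM model in the same section with the same structure, including the pre-intervention volumes.

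A period or sequence term may be added as an optional refinement. No scanner term is needed for an additive shift if each child is scanned on the same machine throughout.

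The cost is revised wording and a different second-level design matrix, with no new data. The change should be settled before connectivity results are seen; at the time of the article the trial was still recruiting.
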